**N/A**

a. If the study has different arms, explain the process for assigning participants (intervention/control, case/control), including the sequence and timing of the assignment.

b. If human biospecimens (blood, urine, saliva, etc.) will be collected, provide details about who will collect the specimen, the volume (ml) and frequency of collection, how the specimen will be used, stored, identified, and disposed of when the study is over. If specimens will be collected for use in future research (beyond this study), complete the Biospecimen Repository section below.

c. If genetic/genomic analyses are planned, address whether the data will be contributed to a GWAS or other large dataset. Address returning unanticipated incidental genetic findings to study participants.

d. If clinical or laboratory work will be performed at JHU/JHH, provide the JH Biosafety Registration Number.

e. If you will perform investigational or standard diagnostic laboratory tests using human samples or data, clarify whether the tests are validated and/or the lab is certified (for example is CLIA certified in the U.S.). Explain the failure rate and under what circumstances you will repeat a test. For all human testing (biomedical, psychological, educational, etc.), clarify your plans for reporting test results to participants and/or to their families or clinicians. Address returning unanticipated incidental findings to study participants.

f. If your study involves medical, pharmaceutical or other therapeutic intervention, provide the following information:

- Will the study staff be blind to participant intervention status?
- Will participants receive standard care or have current therapy stopped?
- Will you use a placebo or non-treatment group, and is that justifiable?
- Explain when you may remove a participant from the study.
- What happens to participants on study intervention when the study ends?
- Describe the process for referring participants to care outside the study, if needed.

**VI. Data Custody, Security, and Confidentiality Protections**

A. Data Storage

| 1. Hard Copies of Data Collection Forms. | |
| --- | --- |
| X | This activity will not involve receiving and/or accessing hard copies of data |
|  | Data collection forms RECORD NO PERSONAL IDENTIFIERS connecting study participants, and there are no codes providing a link. Data are anonymous. |
|  | Data collection forms INCLUDE IDENTIFIERS. The forms are locked in a secure cabinet or room with limited access by authorized individuals. Forms will be kept in study team’s possession during transport and will not be left unattended in a vehicle. When possible, de-identified copies will be used for coding and analysis. |
| X | Data collection forms ARE CODED with study participants’ random study ID numbers. Codes/links between study IDs and identifiers are stored securely in a separate place (locked storage cabinet or secure electronic database.) |
|  | Other: |
| 2. Electronic Data | |
| X | The data do not contain personally identifiable information |
| X | These data are stored on a secure server protected by limited access and strong password systems. Data are coded when possible. Portable electronic devices will not contain identifiable information unless encrypted. |
|  | Other: |
| 3. Other Identifiable Data Storage, Retention, and Destruction (Audiotapes, videotapes, photographs, etc.) will be retained and stored securely (locked in cabinet or room) until: | |
|  | Transcription is complete, then will be destroyed. |
|  | Analysis is complete, then will be destroyed. |
|  | Study is complete and file is closed. |
|  | Indefinitely. Provide justification for indefinite retention: |
| 4. Existing Biospecimens to be used in this study: | |
|  | HAVE NO PERSONAL IDENTIFIERS. |
|  | INCLUDE IDENTIFIERS AND ARE CODED; the PI will not have access to the link or code connecting the identifiers to the specimens. |
|  | INCLUDE IDENTIFIERS, and the PI has access to those identifiers or to the link/code connecting specimens to individuals. The identifiers and/or code will be stored securely until the study is complete. |

B. Certificate of Confidentiality

Will the study data stored in the United States be protected by a Certificate of Confidentiality? If yes, explain who will apply for and maintain the Certificate. (<http://grants.nih.gov/grants/policy/coc/appl_extramural.htm>)

No.

C. Data Security and Sharing

Study data will be collected using encrypted mobile tablets, and completed surveys will be uploaded to a secure server immediately upon completion using mobile hotspots or SIM cards. Servers are maintained by SurveyCTO, a consulting firm that manages large scale survey data studies which is under contract with the GEAS. No data will be stored on the tablets. During the course of the study no identification information will be shared except with data collectors for the explicit purpose of contacting participants for the subsequent wave of data collection. Once coded, electronic data will be shared with the Hopkins study team for purposes of data analysis and report generation. Once the three waves of data collection are complete and data are linked then all electronic data will be de-identified and thus anonymous; reporting will be in the aggregate.

**VII. Risks of the Study**

A. Describe the risks, discomforts, and inconveniences associated with the study and its procedures, including physical, psychological, emotional, social, legal, or economic risks, and the risk of a breach of confidentiality. These risks should be described in the consent documents.

B. Describe the anticipated frequency and severity of the harms associated with the risks identified above; for example, if you are performing “x” test/assessment, or dispensing “y” drug, how often do you expect an “anticipated” adverse reaction to occur in a study participant, and how severe do you expect that reaction to be?

C. Describe steps to be taken to minimize risks. Include a description of your efforts to arrange for care or referral for participants who may need it.

D. Describe the research burden for participants, including time, inconvenience, out-of pocket costs, etc.

E. Describe how participant privacy will be protected during data collection if sensitive questions are included in interviews.

This study involves a low level of risk since this is survey research; however, some of the questions may cause discomfort or a desire for self-disclosure of adverse experiences or exposures. To assure that any issues that arise are addressed in a timely fashion we will collaborate with both Save the Children and Georgetown University/IRH, both of whom have ongoing relationships with youth-serving and child protection agencies in Kinshasa. The protection of vulnerable youth is detailed below (p. 17).

As noted above, some information collected as part of the GEAS is personal, and participants will be informed that this information is confidential and that they have the right to refuse answering questions or sections of the survey without prejudice. Participants will be asked questions about a range of topics including family, school, sexual attitudes and behaviors, mental health, and adverse childhood experiences any of which may make them uncomfortable. It should be noted that the modules on adverse childhood experiences and on sexual and reproductive health will be completed using CASI/ACASI rather than by interviewer so that the data are directly entered by the adolescent into the tablet. As noted previously, data collectors will undergo a 5-day training prior to data collection to learn among other things how to recognize if participants are feeling significant distress. Data collectors will be informed that if an adolescent participant experiences signs of distress, they will immediately remind the participant that they do not need to answer any questions that make them feel uncomfortable. If the respondent decides to stop, the data collector will notify the field coordinator who will notify the respondent’s parent/guardian of the situation. If he/she asks to continue the data collector will do so; however, if discomfort is expressed a second time the data collector will cease data collection and will notify the field coordinator immediately. Additionally, the young person and parent/guardian will be provided resources for help if needed.

In all cases, data collectors will be required to record if a participant experiences distress and inform the field coordinator who will advise the site PI. Where there is suspicion or evidence of physical or sexual abuse the data collector will be instructed to stop the interview, inform the subject of his/her concern and notify the field coordinator and site PI. If the site PI determines that the situation warrants follow up he will contact the designated child protection agency and concurrently notify the Hopkins PI who in turn will notify the JHBSPH IRB detailing the steps being taken to protect the child. Where the abuse may involve a parent or family member the report will go directly to the field coordinator/PI however if it does not, the parent will also be informed. Additionally, a detailed child protection protocol specific to Kinshasa is in place.

1. Describe any potential direct benefits the study offers to participants (“payment” for participation is not a direct personal benefit).

Those in the intervention arm of the study will benefit from an evidence-based program that has been developed and implemented by Save the Children. Previous research suggests that the intervention is effective in increasing gender equitability and shifting gender norm attitudes that benefit participants. We hypothesize that those who will be participants will also be improved contraceptive users and less likely to be perpetrators or victims of gender-based violence.

There is no direct benefit to participants in the control group beyond what has been previously reported as the benefits research subjects feel in being able to share their experiences, exposures and perspectives.

Participants in both groups will be provided a meal and a t-shirt with the study logo.

1. Describe potential societal benefits likely to derive from the research, including value of knowledge learned.

The evidence is that gender-based violence is endemic in the DRC and the direct hypothesized benefit is that the intervention will reduce GBV by 20% and double effective contraception. Additionally, we hypothesize that there will be secondary benefits of more gender equitable relationships between boys and girls in the intervention group, improved mental health outcomes and an increase in healthy sexuality and school retention.

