Given the longitudinal nature of the study and the fact that it is confidential but not anonymous, special procedures will be undertaken so as to assure that data are secure and that participants can be assured of absolute confidentiality (see Section VI below for procedures). Additionally, since sensitive data will be collected including data indicating potential exposure to gender-based violence and abuse, participants will be advised in advance that reporting of certain events may result in a report to authorized child protection services.

Thus, during the consent process we will be explicit with both potential participants and their parents about what kind of information will be collected. Specifically, participants will be assured that information will be confidential and will not be shared except in cases of exposure to sexual or physical abuse that requires notification to authorities. In such cases data collection will cease immediately, and, with the permission of the adolescent participant (when the event involves those other than parents and immediate family), parents will be informed and the data collector will notify his or her filed coordinator who in turn notifies the site-PI ([name]), who will then prepare the report to the appropriate organization and/or agency. At that point the Hopkins study PI ([name]) will also be notified and in turn he will notify the JHBSPH IRB in accordance with JHU guidelines. When the events involve a parent or close family member, notification will go to a pre-selected organization tasked with protection of children and minors, who will pursue the investigation and the remainder of the reporting process will remain unchanged.

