D**.** Reporting unanticipated problems/adverse events (AE’s) to the IRB (***all studies must complete this section***):

Describe your plan for reporting to the IRB and (if applicable) to the sponsor. Include your plan for government-mandated reporting of abuse or illegal activity.

As noted previously, the protocol of the study requires that if the data collector suspects that the participant is distressed then the data collector will ask the study participant if the observation is correct. If no, then the data collection will continue. If yes, then the participant will be asked if she/he wants to continue. If no, then the data collection will cease, the participant will be provided information on where she/he might seek help and the data collector will notify the field coordinator. If the data collection continues and if in the opinion of the data collector distress continues then the data collection will cease and the same procedure as noted above will be followed. If there is suspected abuse then the protocol will be followed as described in Section VII.

Whenever a report of suspected child abuse is made, the site PI will notify the study PI ([name]) who in turn will notify the JHBSPH IRB as well as the University Counsel both of the event and subsequently of the disposition.

NOTE: The IRB does not require submission for all AEs, only those that are **unanticipated, pose risk of harm to participants or others, and are related to the study**.

E. Other IRBs/Ethics Review Boards:

If other IRBs will review the research, provide the name and contact information for each IRB/ethics review board and its Federal Wide Assurance, if it has one (available on OHRP’s website at <http://www.hhs.gov/ohrp/assurances>).

This study will be reviewed and approved by the Kinshasa School of Public Health Institutional Review Board.

F. Collaborations with non-JHSPH Institutions:

For studies that involve collaboration with non-JHSPH institutions, complete the chart below by describing the collaboration and the roles and responsibilities of each partner, including the JHSPH investigator. This information helps us determine what IRB oversight is required for each party. Complete the chart for all multi-collaborator studies.

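### The escalation rules for a distressed or abused adolescent disagree on when a parent is told and whether the adolescent must permit it, and partly on who decides about referral

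*Protocol*

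**What the plan says.** Three places in the protocol set out what happens when an adolescent is distressed or abuse comes to light: the Consent Process text in Section V, Section VII (Risks of the Study), and the later part D on reporting unanticipated problems and adverse events to the IRB.

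**Distress without disclosed abuse.** Section VII: "If the respondent decides to stop, the data collector will notify the field coordinator who will notify the respondent’s parent/guardian of the situation". If the adolescent carries on and becomes uncomfortable again, "if discomfort is expressed a second time the data collector will cease data collection and will notify the field coordinator immediately". Section VII adds that help resources go to both the adolescent and the parent or guardian if needed. Part D, presenting itself as a restatement, says of a stop that "the participant will be provided information on where she/he might seek help and the data collector will notify the field coordinator". It applies the same steps when distress continues later in the interview, and it mentions no parent.

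**Abuse by someone outside the family.** Consent Process: "with the permission of the adolescent participant (when the event involves those other than parents and immediate family), parents will be informed". Section VII first deals with abuse that may involve a parent or relative and then adds: "however if it does not, the parent will also be informed".

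**Referral, and abuse within the family.** Under the Consent Process text, the site PI is the person "who will then prepare the report to the appropriate organization and/or agency", and in family cases "notification will go to a pre-selected organization tasked with protection of children and minors". Section VII directs family cases to the field coordinator or PI and says: "If the site PI determines that the situation warrants follow up he will contact the designated child protection agency". In that sentence, notice to the Hopkins PI, and through that PI to the IRB, accompanies the agency contact.

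Part D refers suspected abuse back to Section VII. A child protection protocol specific to Kinshasa is listed as an appendix; its text is not among the documents at hand.

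**The concern.** The participants are 10 to 14 years old at enrolment, are surveyed every six months, and are asked about adverse childhood experiences and gender-based violence. Field staff need one instruction for each situation, and the protocol gives more than one.

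The three inconsistencies carry different risks:

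- In non-family abuse, a parent may be told against the adolescent's wishes, although the Consent Process text makes that depend on permission.
- In a distress stop, a parent may be told that the child broke off the interview when that parent is the reason for the distress.
- In referral, the same facts might or might not reach a child-protection body and the IRB, depending on which section is followed.

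The Consent Process text also describes confidentiality with one exception, abuse that has to be reported. Telling a parent about a distress stop falls outside that exception, even if none of the child's answers are passed on.

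**Working it through.** No arithmetic applies. The check sets the three texts side by side for each situation.

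| Situation | Consent Process (Section V) | Section VII | Part D (reporting to the IRB) |
| --- | --- | --- | --- |
| Distressed adolescent stops | Not covered | Coordinator told; coordinator tells parent or guardian, no condition | Help information to adolescent; coordinator told; no parent contact |
| Distress recurs after continuing | Not covered | Interview ends; coordinator told; resources to adolescent and parent if needed | Same steps as for the first stop |
| Abuse, non-family | Parents told if the adolescent permits | Parent told; no permission step | Refers to Section VII |
| Abuse, parent or relative | Notice to a child-protection organization; rest of the process unchanged | Report to field coordinator or PI; parent not told | Refers to Section VII |
| Contact with the agency | Site PI prepares the report once abuse requires notification | Site PI decides whether follow-up is warranted | Refers to Section VII |
| Notice to the IRB | Follows from the site PI's report | Tied to the same decision by the site PI | Follows whenever a report of suspected abuse is made |

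**Non-family abuse.** Suppose the adolescent refuses permission. The Consent Process text then does not allow the parents to be told, and Section VII has them told. No action satisfies both. Part D does not break the tie: it defers to Section VII without saying that Section VII overrides the Consent Process text.

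**Distress stop.** Section VII makes parent notification a required step. Part D claims to repeat the procedure and leaves the step out. Staff working from part D alone would not contact the parent. Section VII is also uneven within itself: it names notification at a voluntary stop, but only the coordinator and conditional resources when discomfort recurs.

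**Parent as possible cause.** Section VII's abuse branch begins at suspicion and separates out the family case. Its distress branch has no matching provision. The module on adverse childhood experiences is self-entered on the tablet, so the data collector may see only distress and a stop. If nothing has been disclosed and no suspicion has formed, the distress branch applies, and under Section VII the parent or guardian is notified whoever caused the distress.

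**Referral.** The Consent Process text has its own threshold: it speaks of abuse that requires notification to authorities. Once that is met, the site PI's report follows. Section VII states the step as the site PI's determination. The named recipient of a family-abuse report also differs. These texts can be read together in part, so this is the weakest of the three conflicts.

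**The case against.** The strongest reply has four parts.

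**Part D is a summary written for another purpose.** It answers a question about reporting to the IRB, and its silence on parents does not forbid telling them. That is fair. On distress stops the two texts differ in completeness and do not flatly contradict each other. The reply does not touch the permission conflict, which lies between the Consent Process text and Section VII, nor the missing provision for a parent who may be the cause.

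**The referral texts can be joined into one chain.** The data collector tells the coordinator, the coordinator tells the site PI, and the site PI tells the agency. Section VII may only be saying who applies the threshold. This largely stands. What remains is that a reader must construct that reading, that the stated recipients differ, and that IRB notice is worded differently in each place.

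**The child protection appendix may settle everything.** It may give further rules, and staff are trained in managing and reporting abuse and have access to a child-protection counselor. These points reduce certainty about what would happen in the field. They do not make the three passages agree, and part D sends staff to Section VII, not to the appendix.

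**The harm is easily overstated.** A reader might infer that all three inconsistencies expose a child abused at home to that parent. The documents do not support this. The permission conflict concerns abusers outside the family, and the referral conflict bears on whether a case is reported. Once family abuse is suspected, neither the Consent Process text nor Section VII tells the parent. Exposure arises only through the distress-stop rule, when the child has disclosed nothing and no suspicion has formed. Even then, the coordinator makes the contact, and the parent is told of the situation, not of the child's answers.

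**Conclusion.** The escalation rules are inconsistent as written and need reconciling. One contradiction is direct: permission for telling parents about non-family abuse. One is a mismatch between two accounts of the distress-stop procedure, together with silence on a parent who may be the cause. One is partial: the recipient of family-abuse reports, and whether referral and IRB notice follow automatically or on the site PI's determination.

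No number of affected children can be given. A reader might be tempted to apply the 10% gender-based violence rate in Table 3 to the cohort and take a share for household abuse. That would count the wrong children: those whose household abuse is recognised enter the family branch, where neither text informs the parent. The protocol gives no frequency for distress stops or for disclosures of non-family abuse.

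A reader might also infer that the rules bias the gender-based violence outcome downward through under-reporting. The protocol offers nothing to establish or size such an effect, and this point does not rest on it.

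The conclusion rests on the protocol text alone. The unseen appendix could add rules but would leave the conflicts in the main text standing.

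**What to change.** Reconcile the Consent Process text, Section VII and part D into a single decision path, and bring the consent, assent, training and child-protection texts into line with it. For each of three situations (distress stop, abuse by a non-family person, abuse by a parent or relative), the path should state:

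- who is told, in what order and by whom;
- whether the adolescent's permission is needed before a parent is told;
- whether referral to the agency and notice to the IRB are automatic or left to the site PI's determination.

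It should also say explicitly whether the distress path makes an exception where a parent may be involved. The sponsor and its child-protection partner decide which rule applies in each case; this review takes no position on that. One section should hold the full path, and the others should refer to it without restating it.

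The cost is a protocol amendment with matching wording in the related documents, reviewed by the two ethics boards named in the protocol, and a briefing within training that is already planned. Sample size, data collection and analysis do not change.
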